## Abstract

**Background:**

Second-generation everolimus-eluting stents (EES) and third generation biolimus-eluting stents (BES) have been shown to be superior to first-generation paclitaxel-eluting stents (PES) and second-generation sirolimus-eluting stents (SES). However, neointimal proliferation and very late stent thrombosis is still an unresolved issue of drug-eluting stent (DES) implantation overall. The Absorb™ (Abbott Vascular, Abbott Park, IL, USA) is the first CE approved DES with a bioresorbable vascular scaffold (BVS) thought to reduce long-term complication rates. The EVERBIO II trial was set up to compare the BVS safety and efficacy with both EES and BES in all patients viable for inclusion.

**Methods/Design:**

The EVERBIO II trial is a single-center, assessor-blinded, randomized trial. The study population consists of all patients aged ≥18 years old undergoing percutaneous coronary intervention. Exclusion criterion is where the lesion cannot be treated with BVS (reference vessel diameter >4.0 mm). A total of 240 patients will be enrolled and randomly assigned into 3 groups of 80 with either BVS, EES or BES implantation. All patients will undergo a follow-up angiography study at 9 months. Clinical follow-up for up to 5 years will be conducted by telephone. The primary endpoint is in-segment late lumen loss at 9 months measured by quantitative coronary angiography. Secondary endpoints are patient-oriented major adverse cardiac event (MACE) (death, myocardial infarction and target-vessel revascularization), device-oriented MACE (cardiac death, myocardial infarction and target-lesion revascularization), stent thrombosis according to ARC and binary restenosis at follow-up 12 months angiography.

**Discussion:**

EVERBIO II is an independent, randomized study, aiming to compare the clinical efficacy, angiographic outcomes and safety of BVS, EES and BES in all comer patients.

**Trial registration:**

The trial listed in clinicaltrials.gov as NCT01711931.

## Background

Drug-eluting stents (DES) have considerably reduced neointimal hyperplasia and significantly decreased the risk of restenosis compared to bare metal stents (BMS) [1]. However, the persistent polymer within the vessel lumen has been held responsible for ongoing endothelial inflammation, incomplete endothelialization and subsequent atherosclerosis, all leading to late complications such as restenosis and stent thrombosis [2].

Everolimus-eluting stents (EES) and biolimus-eluting stents (BES) are more recent DES that have been widely investigated. The EES is at present the most frequently used DES in the USA and in Europe [3]. It was demonstrated as non-inferior to sirolimus-eluting stents (SES) in the ISAR-TEST IV and the EXCELLENT trial and superior to paclitaxel eluting stents (PES) in two large randomized studies (Spirit-IV and COMPARE) [4-7]. One propensity score matched registry (LESSON-1) showed a trend towards a lower risk of death, myocardial infarction (MI) and target-vessel revascularization (TVR) as compared to SES over a 3-year follow-up [8].

BES differs from EES in that it possesses an abluminal polymer coating that is completely converted to lactic acid in 6 months and, via the Krebs cycle, to carbon dioxide and water in 6 to 9 months. Two large clinical trials (NOBORI and LEADERS) proved its non-inferiority to PES and SES at 9 months and 4 years, respectively [9,10]. The propensity score matched EVERBIO trial showed similar risk of death, MI and TVR in BES compared to EES during a 2-year follow-up [11]. Recently, the randomized COMPARE II trial enrolling 2,707 patients, confirmed the BES safety but no differences were observed in clinical endpoints at 2-year follow-up when compared to EES [12]. The ongoing Global LEADERS trial with an expected inclusion of >10,000 patients will provide further information on BES. The lactic acidification of the media from the polymer could impact vascular healing at the stent vicinity and promote a deleterious inflammatory reaction [13].

The unresolved problem of neointimal proliferation and very late stent thrombosis from lingering polymers and vascular scaffolds, led to the development of new-generation completely resorbable stents. The Absorb™ (Abbott Vascular, Abbott Park, IL, USA) is the first CE approved DES with a bioresorbable vascular scaffold (BVS). It uses a poly-l-lactide polymer that is absorbed after approximately 2 years via the Krebs cycle. A prospective, open-label, 2-stage study called ABSORB including 131 patients was conducted in Europe and New Zealand and led to its approval by the EU in January 2011 for the treatment of coronary artery lesions [14]. The major adverse cardiac event (MACE) rate was reported as 6.8% at 2-years follow-up and late lumen loss (LLL) 0.27 mm at 12 months [15,16]. Its non-inferiority to the Xience Prime (Abbott Vascular), an EES, is currently under investigation in the international ABSORB EXTEND trial that plans to enroll 1,000 patients (NCT01023789). To date, there is no data on BVS compared to EES or BES, and independent trials are eagerly awaited. We seek to compare the efficacy and safety profiles of these three different types and generations of DES.

### Study objectives and hypothesis

The purpose of the EVERBIO II trial is to evaluate the efficacy, angiographic outcome and safety of three different stents in *de novo* coronary artery lesions: the BVS Absorb™ (Abbott Vascular), the EES Promus Element™ (Boston Scientific, Natick, MA, USA) and the BES Biomatrix Flex™ (Biosensors International Ltd., Morges, Switzerland). The null hypothesis to be rejected is that all three stents are of equal efficacy. We believe there will be a significant difference with regard to LLL at 9 months and a clinical endpoint of death, MI and TVR at 12 months between EES and BES and BVS stents.

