### Statistical analyses

We plan to enroll 80 patients in each group. Comparison between EES and BES with BVS will necessitate a total of 240 patients in order to achieve a power of 90% to prove a difference of 0.2 mm LLL at 9 months (BES and EES = 0.3 mm vs BVS 0.5 mm; SD 0.5 mm). This allows for a dropout rate of 20% of the sample in which case the study would still yield a power of 83%. Sample size calculations were performed using Sample Power 3 (SPSS Inc, Chicago, IL, USA) at a two-tailed significance level of α = 0.05.

Continuous variables are presented as mean ± standard deviation or median (25% to 75%) interquartile range according to their distribution. Categorical variables are presented as counts and percentages. Comparison between the individual groups and comparison between BES and EES and BVS are performed on demographical data and risk factors as well as on procedural characteristics. The primary outcome is analyzed using a parametric or nonparametric test according to distribution and by the computation of a multivariate linear analysis by taking into account significant risk factors that potentially influence outcome thus adjusting for them. Clinical endpoints are compared using the Kaplan-Meier method. Binary logistic regression is equally performed in the search of independent predictors for the secondary endpoints. All analyses are performed according to the intention-to-treat principle. An intermediate analysis will be performed after follow-up angiography of 40 patients in each group.

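### The stated null is equality of all three stents, but the trial is sized on BVS against EES and BES combined, and the primary analysis names neither test; testing the null as written has 74% power

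*Protocol article*

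**What the plan says.** Three places in the protocol article bear on which test decides the trial.

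- **Study objectives and hypothesis.** The null is global: "The null hypothesis to be rejected is that all three stents are of equal efficacy". The expectation that follows is a difference "between EES and BES and BVS stents". That wording can be read as three groups, as pairs, or as the two metallic stents together against BVS.
- **Statistical analyses, sample size.** "We plan to enroll 80 patients in each group". "Comparison between EES and BES with BVS will necessitate a total of 240 patients", the aim being "to prove a difference of 0.2 mm LLL at 9 months". The assumptions are "BES and EES = 0.3 mm vs BVS 0.5 mm; SD 0.5 mm", so EES and BES share one mean. The stated power is 90%, or 83% if 20% drop out, at a two-tailed alpha of 0.05.
- **Statistical analyses, primary outcome.** A parametric or nonparametric test is chosen by distribution, with an adjusted linear model alongside. No contrast is named.

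One further sentence in Statistical analyses, "Comparison between the individual groups and comparison between BES and EES and BVS are performed", goes on to confine those comparisons to baseline patient data and procedural variables. It does not concern LLL.

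**The concern.** The null and the sample size point to different tests. An analyst following the hypothesis section would run a three-group test. One following the sample-size paragraph would run a single contrast of BVS with the other two stents combined. The primary-outcome sentence does not settle it. The tests differ in power at the same sample size and answer different questions, so the stated power cannot be attached to the test of the null as written. With the choice left open, the deciding comparison could also be picked after the LLL results are known.

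**Working it through.** **Inputs** (Statistical analyses): means 0.3 (EES), 0.3 (BES) and 0.5 mm (BVS); SD 0.5 mm; two-sided alpha 0.05; 80 per group. A 20% dropout leaves 0.8 × 80 = 64 per group.

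**1. The plan's own figures, from the combined contrast (80 v 160, or 64 v 128).**

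- 80 per group: SE = 0.5 × √(1/80 + 1/160) = 0.0685; 0.2/0.0685 = 2.92; power ≈ Φ(2.92 − 1.96) = 83.2% (t-distribution 82.9%).
- 64 per group: SE = 0.5 × √(1/64 + 1/128) = 0.0765; 0.2/0.0765 = 2.61; power ≈ Φ(2.61 − 1.96) = 74.3% (t: 73.9%).

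So 90% and 83% are not reproduced at the stated two-sided level. Two readings recover the pair, and both use the combined contrast:

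- One-sided 0.05: Φ(2.92 − 1.645) = 89.9% and Φ(2.61 − 1.645) = 83.3%.
- Two-sided with 100 per group, giving about 90% and falling to about 83% when 20% loss leaves 80.

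The article does not say which, if either, was used.

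**2. The null as written: three-group F-test.** The grand mean is (0.3 + 0.3 + 0.5)/3 = 0.3667.

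- λ = 80 × [2 × (0.3 − 0.3667)² + (0.5 − 0.3667)²]/0.5² = 8.53. On 2 and 237 df, power is 74.1%.
- With 64 per group, λ = 6.83. On 2 and 189 df, power is 63.6%.

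Here λ equals the square of the combined contrast's noncentrality (2.92² ≈ 8.53). The signal is the same, but the F-test spreads it over two degrees of freedom, which is where the power goes.

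**3. One pairwise BVS test.**

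- 80 v 80: SE = 0.5 × √(2/80) = 0.0791; ratio 2.53; power 71.6% (t: 71.0%).
- 64 v 64: SE = 0.0884; ratio 2.26; power 61.9% (t: 61.2%).

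Both BVS comparisons are significant together in about 58% and 46% of trials (simulation, 200,000 runs).

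**4. Summary (t and F distributions).**

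| Test, two-sided 0.05 | 80 per group | 64 per group |
|---|---|---|
| Stated in the article | 90% | 83% |
| BVS v EES+BES combined | 82.9% | 73.9% |
| Three-group F-test | 74.1% | 63.6% |
| One pairwise BVS test | 71.0% | 61.2% |

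**5. Splitting the gap for the F-test.**

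- 80 per group: 90 − 74.1 ≈ 16 points. About 7 (90 − 82.9) come from the stated power not holding at two-sided 0.05, and about 9 (82.9 − 74.1) from the change of test.
- 64 per group: 83 − 63.6 ≈ 19 points, of which about 9 and about 10 respectively.

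**6. Sensitivity to EES = BES.** Suppose, as an assumption, means of 0.3, 0.4 and 0.5 mm. The F-test then has 60.8% (50.7%). The combined contrast sees 0.5 − 0.35 = 0.15 mm, a ratio of 0.15/0.0685 = 2.19, and about Φ(2.19 − 1.96) = 59%. The advantage of the combined contrast therefore depends on EES and BES having similar means, as the article assumes.

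**The case against.** The strongest reply is that no real conflict exists. If all three means are equal, BVS equals the average of the other two. The combined contrast is therefore a valid 5% test of the stated null, and rejecting it rejects that null. A one-degree-of-freedom contrast aimed at the expected pattern is ordinary practice, and under that pattern it beats the F-test (83% against 74%). The sample-size sentence already implies it, and a condensed article may leave the formal label to the full protocol or the analysis plan.

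Most of this stands. It rules out saying that the powered contrast fails to test the stated null, or that the article gives no indication of a contrast. It does not remove the point. Nothing in the article designates the combined contrast as the primary test, and the null is worded for the three-group test, which lacks the stated power. The combined contrast is also narrower: it would miss EES and BES differing in opposite directions around BVS. An analysis plan that chose one test would have to depart from one of the two statements as they now read.

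A reader might go further and infer that pairwise and combined tests of LLL are all planned at 0.05, which would inflate the type I error. The article does not support this. The sentence listing both kinds of comparison is about baseline and procedural data, and no set of tests is laid down for the primary endpoint. No familywise error figure should be claimed.

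A reader might also charge the whole 16-point or 19-point shortfall to the mismatch. Only about 9 to 10 points belong to it.

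**Conclusion.** The point holds as an inconsistency between the stated null and the sample size, left unresolved by the primary analysis. Applying the three-group test that the null's wording suggests costs about 9 points of power at full enrolment and about 10 after 20% dropout, compared with the contrast on which the trial was sized. A single pairwise BVS test costs about 12 to 13 (82.9 − 71.0 and 73.9 − 61.2). Separately, the contrast on which the trial was sized has about 83% (74%) power, not 90% (83%), at the stated two-sided level.

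These figures rest on the article's own means and SD, equal group sizes, dropout spread evenly over the groups, and an unadjusted comparison of means. The size of the loss depends on EES and BES having the same mean. The type I error of the planned primary analysis is not shown to be inflated.

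**What to change.** In Study objectives and hypothesis, state the primary null as: mean 9-month LLL with BVS equals mean 9-month LLL with EES and BES pooled. In Statistical analyses:

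- Name that contrast as the single primary test, at two-sided 0.05.
- Restate its power as about 83%, or about 74% after 20% dropout.
- Only if it is rejected, test BVS against EES and BVS against BES, each at two-sided 0.05. This is a closed procedure: if both pairwise nulls are true the pooled null is true, so the gate protects both at 5%. With a common SD, two pairwise wins in the same direction always carry the pooled test, because its standard error is smaller (0.0685 against 0.0791). The gate therefore never blocks a double win.
- Label EES against BES exploratory.

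The cost is about one paragraph across the two sections. Trial status reports recruitment complete, so the sample size can no longer be raised to recover 90%. The change should be dated before LLL is compared by group. There are two downsides: no pairwise BVS claim can be made if the pooled test fails, and the published power becomes less favourable.

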## Methods/Design

### Study design and overview

This is a single center, assessor-blinded, randomized study comparing three different stents in *de novo* coronary lesions: the Absorb™, the Promus Element™ and the Biomatrix Flex™. The protocol of the trial has been registered online (NCT01711931) at http://www.clinicaltrials.gov. Figure 1 briefly summarizes the main study steps and Table 1 the longitudinal follow-up. The organization and scientific conduct is supervised by a Steering Committee. A Data and Safety Monitoring Board is responsible for safety and ethical aspects. A Clinical Events Adjudication Committee (CEAC) including interventional and non-interventional cardiologists review and adjudicate all reported events and endpoints and perform computation and angiographic measurements. All members of the CEAC are blinded to the primary results of the trial. The study complies with the Declaration of Helsinki and was approved by the local ethics committee of Fribourg University and Hospital (Switzerland, 043/12-CER-FR).

**Figure 1 F1:**
[figure not shown]
**Study algorithm.** BES: biolimus-eluting stent, BVS: biovascular scaffold, EES: everolimus-eluting stent, OCT: optical coherence tomography, PCI: percutaneous coronary intervention. ^a^Primary endpoint: late lumen loss at 9-month angiography study. ^b^Secondary endpoints: patient oriented (death, myocardial infarction, target vessel revascularization), device oriented (cardiac death, myocardial infarction, target-lesion revascularization), stent thrombosis, binary restenosis at 9-month angiography study.

**Table 1 T1:** Timetable of prospective investigations

**Investigation**	**Baseline**	**Post procedure**	**3 months**	**6 months**	**9 months**	**12 months**	**2 years**	**5 years**
Medical/clinical history	x	x	x	x	x	x	x	x
Physical examination	x	x			x			
12-lead ECG^a^	x	x			x			
Coronary angiogram^b^	x				x			
Procedural complications		x			x			
Laboratory survey^c^	x				x			
CK, CK-MB, troponin^d^		x			x			
Medications	x	x	x	x	x	x	x	x
Primary outcome					x			
Secondary outcome			x	x	x	x	x	x

^a^Any ECG may be obtained when clinically relevant.

^b^Unscheduled angiograms after 6 months will be considered 9-month follow-up angiograms.

^c^Usual laboratory survey include, complete blood count, electrolytes, fasting glucose level, INR, prothrombin time, partial thromboplastin time, creatinine, blood urea nitrogen, pregnancy test if applicable.

^d^All patients will benefit from cardiac enzyme measurement 4 h post procedure, enzymes may be followed every 8 h if clinically relevant and at the discretion of the operator.

*CK* creatine kinase, *ECG* electrocardiogram.

### Study endpoints

The primary endpoint is LLL at 9 months as assessed by quantitative coronary angiography. The secondary endpoints are divided in angiographic and clinical findings. We will assess angiographic success, device success and binary restenosis at 9 months. Clinical endpoints include a patient-oriented MACE (composite of death, MI and TVR) a device-oriented MACE (composite of cardiac death, MI and target lesion revascularization (TLR)) and stent thrombosis (ST) at 6 months, and 1, 2 and 5 years.

### Patient selection criteria

All patients aged ≥18 years undergoing coronary angiography at the University & Hospital Fribourg (Switzerland) for suspected coronary artery disease on functional cardiac testing, stable angina or acute coronary syndrome (unstable angina, non-ST segment MI, ST-elevated MI) are eligible. Patients must be apt and willing to provide written informed consent and participate in follow-up. Patients with a known or presumed hypersensitivity to heparin, antiplatelet drugs and hypersensitivity to contrast dye not controllable with standard premedication will be excluded. Patients are recruited on the day of their angiography by one of the investigators if all inclusion criteria are met and no exclusion criteria apply. Written informed consent will be obtained as required by the local institutional ethics committee in accordance with the Declaration of Helsinki.

### Treatment assignment

Patient randomization will be performed after lesion preparation. Exclusion criterion is when the lesion cannot be treated with BVS (reference vessel diameter >4.0 mm). Randomization will be completed via computer-generated numbers. Allocation concealment will be kept in sealed envelopes containing a non-transparent pleated color sheet in which the etiquette for intervention is embedded. The investigator is responsible for enrolment and a study nurse will assign participants to either stent implantation. Only the outcome assessors and data analysts are blinded to the intervention.

### Index percutaneous coronary intervention

Procedures will be performed via the femoral or radial artery with a 5-6 French (F) guiding catheter. Standard interventional techniques will be used and performed according to practice guidelines. Preprocedural antithrombotic regimen is systematically achieved with aspirin (500 mg intravenous bolus for those not under treatment and 100 mg for those already under aspirin and then 100 mg/day for all) and unfractionated heparin (70 UI/kg), whereas glycoprotein IIb/IIIa inhibitors are used per operator discretion. All patients will receive either a minimum 600 mg loading dose of clopidogrel, 180 mg of ticagrelor, or 60 mg prasugrel before or immediately after the procedure. Lifelong ≥100 mg daily aspirin and either 75 mg daily clopidogrel, or 90 mg twice-daily ticagrelor or 10 mg prasugrel for a minimum of 6 months will be prescribed. Other medications will be prescribed as per standard of care. All patients will be monitored between 4 to 12 h in an intermediate care unit and will undergo baseline and 3 to 6 h cardiac biomarker measurements. A standard 12-lead electrocardiogram (ECG) is recorded immediately after the procedure and with each biomarker measurement.

### Follow-up coronary angiography

Effectiveness will be measured at the 9-month follow-up angiography in all patients. Quantitative measures will be performed within the stent and the 5 mm edge region. In-segment LLL will be defined as the difference between the minimum lumen diameter post procedure and at 9 months. Binary restenosis will be defined as >50% diameter stenosis. LLL is computed through quantitative coronary angiography with the use of automated edge-detection system (CAAS II, Pie Medical Imaging, Maastricht, The Netherlands). Any unscheduled angiogram after 6 months will be considered as 9-month follow-up angiogram.

Optical coherence tomography (OCT) is conducted in the first 30 patients of each group willing to undergo the aforementioned procedure. Percentage of malapposed struts, frequency of abnormal intrastent tissue, frequency of peristrut low intensity area and percent net volume obstruction will be assessed with the use of automated edge-detection system (Illumien-optis ORW, St. Jude Medical, St. Paul, MN, USA).

### Clinical follow-up

Patients will be followed clinically by clinic visits or by telephone interview at 3, 6, 9 and 12 months, and 2 and 5 years. No blinding will be present during the collection of outcome data. If the patient is not accessible, data can be retrieved from the referring physician or the hospital electronic database.

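### Clinical outcomes are collected unblinded and only then adjudicated, so blinded assessment does not protect against device-dependent event capture; the committee's blind should be stated as a blind to device

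*Protocol article*

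**What the plan says.** The relevant statements stand in four sections of the protocol article's Methods/Design.

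- **Study design and overview** gives the label: "This is a single center, assessor-blinded, randomized study comparing three different stents". The CEAC is to "review and adjudicate all reported events and endpoints and perform computation and angiographic measurements". Its blind is described in one sentence: "All members of the CEAC are blinded to the primary results of the trial".
- **Treatment assignment** says who is blinded to the stent: "Only the outcome assessors and data analysts are blinded to the intervention". It does not say whether the CEAC members are those outcome assessors.
- **Clinical follow-up** sets the contacts: "Patients will be followed clinically by clinic visits or by telephone interview at 3, 6, 9 and 12 months, and 2 and 5 years". It then states: "No blinding will be present during the collection of outcome data". For a patient who cannot be reached, "data can be retrieved from the referring physician or the hospital electronic database".
- **Trial interruption** ties halting to the incidence of clinical endpoints at the intermediate analysis and to adverse events above expectation at any time. The safety board and the adjudication committee keep an unblinded principal investigator continuously informed, and that investigator alone decides.

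Under Study objectives and hypothesis, the composite of death, MI and TVR at 12 months stands beside late lumen loss (LLL) as an outcome on which the devices are expected to differ.

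**The concern.** An event passes through two steps before it is counted. Someone has to learn of it and report it, and then the committee has to classify it. Blinding the second step removes bias in classification only. If reporting differs by device, the difference is already in the set of events that the committee receives.

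Here the first step is open by design. The interviewer may know the stent and, since only assessors and analysts are blinded, so may the patient. The trial compares a new scaffold with two established stents, and a wish to look harder in one arm is plausible. The documents do not tell us which arm that would be.

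Two uses of these events are at stake: the comparison of patient-oriented and device-oriented MACE and stent thrombosis, and the event counts on which halting depends.

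The second matter is wording. The blind that matters for adjudication is to the device. The one sentence about the committee's blind names something else, namely results that rest on the committee's own measurements.

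**Working it through.** The plan gives no figure on this point, so there is none to reproduce. The check is a reading of the sections together, followed by an illustration of size.

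**Step 1: who is blinded at which step.**

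| Step | Status in the article | Section |
|---|---|---|
| Collecting clinical outcome data | Not blinded | Clinical follow-up |
| Assessing outcomes | Blinded to the stent | Treatment assignment |
| Data analysis | Blinded to the stent | Treatment assignment |
| CEAC adjudication and angiographic measurement | Blinded to the primary results; device not mentioned | Study design and overview |
| Decision to halt | Not blinded | Trial interruption |

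The first two rows are compatible, because collecting and assessing are different steps. The gap is in the first row, which nothing later in the chain can repair. The fourth row needs aligning with the second.

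**Step 2: which endpoints are exposed.** MI, suspected stent thrombosis and indications of revascularisation between scheduled examinations depend on someone asking or reporting. All-cause death depends on this very little. The primary endpoint comes from angiography planned for every patient at 9 months, measured as follows: "LLL is computed through quantitative coronary angiography with the use of automated edge-detection system". It is touched only indirectly, since an unscheduled angiogram after 6 months stands in for the 9-month one.

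**Step 3: illustration of size.** The assumptions, none of them from the documents, are a true event rate p that is equal in all arms (0.10 or 0.20), full capture in one arm, and a capture fraction c of 0.80 or 0.90 in the other.

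- Apparent rate ratio = 1/c.
- Apparent difference = p × (1 − c).
- Events missed in an arm of 80 = 80 × p × (1 − c).

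| p | c | Apparent ratio | Apparent difference | Events missed in an arm of 80 |
|---|---|---|---|---|
| 0.10 | 0.90 | 1/0.90 = 1.11 | 0.10 × 0.10 = 0.01 | 0.8 |
| 0.10 | 0.80 | 1/0.80 = 1.25 | 0.10 × 0.20 = 0.02 | 1.6 |
| 0.20 | 0.90 | 1.11 | 0.20 × 0.10 = 0.02 | 1.6 |
| 0.20 | 0.80 | 1.25 | 0.20 × 0.20 = 0.04 | 3.2 |

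**Step 4: comparison with chance variation.** For the scaffold arm against the two other arms together (80 against 160, from Statistical analyses), the standard error of a difference in proportions is about √[p(1 − p)(1/80 + 1/160)].

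- p = 0.10: √(0.09 × 0.01875) = 0.0411. The false difference is 0.01/0.0411 = 0.24 to 0.02/0.0411 = 0.49 standard errors.
- p = 0.20: √(0.16 × 0.01875) = 0.0548. The false difference is 0.02/0.0548 = 0.37 to 0.04/0.0548 = 0.73 standard errors.

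A shift of z standard errors changes the two-sided 5% error rate to Φ(−1.96 + z) + Φ(−1.96 − z). For z = 0.24 this is about 5.7%. For z = 0.73 it is about 11.3%.

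**The case against.** The strongest reply is that open collection with blinded assessment is a recognised design and that the article discloses it. That is right. A reader might infer that the assessor-blinded label is false, but the documents do not support this. Unblinded collection limits the label to adjudication, measurement and analysis; it does not contradict it.

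The reply continues that the CEAC adjudicates and measures, so its members are naturally the outcome assessors whom Treatment assignment blinds to the stent. The sentence about primary results may then refer to the comparison between arms, as an addition. This reading is reasonable, and it reduces the second part of the point to a request for alignment. The request stands, because the article never makes the link and because the committee also watches event incidence and informs an unblinded investigator.

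No section says that an interviewer filters events before they reach the committee. Examinations at 9 months are the same in every arm, and hospital records can be used when a patient cannot be reached. So selective capture is a risk that the design leaves open, not something shown to happen. What remains exposed is mainly MI and suspected thrombosis between visits, and leads to revascularisation.

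A reader might also infer that LLL is biased because the person measuring could recognise the device and adjust contours. The documents do not support that. They specify automated edge detection, describe no manual correction, call only the biolimus stent metallic in so many words, and say nothing on whether any device can be told apart on film.

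Lastly, operational detail such as interview scripts often sits in a charter or manual, and its absence from an article is no fault. The point here rests on what the article states, namely unblinded collection.

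**Conclusion.** The point holds for the secondary clinical endpoints. Unblinded collection followed by adjudication of reported events leaves MI, suspected stent thrombosis and revascularisation leads open to capture that differs by device, and blinded assessment does not close that gap. The description of the committee's blind is poorly worded and should name the device.

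The size is unknown. Under the assumed capture fractions, equal event rates would appear as a ratio of 1.11 to 1.25, a shift of 1 to 4 percentage points. In the 80 against 160 comparison this is less than one standard error. It would not usually produce a significant result alone, but it could raise the false-positive rate from 5% to between about 6% and 11%. These figures show what modest unequal capture could do; they are no evidence that it occurred or in which direction.

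Severity is minor to moderate. The primary endpoint is not materially affected. The clinical endpoints still matter because the hypothesis names them and the halting decision uses them.

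**What to change.** 1. **Clinical follow-up.** For all remaining contacts, use one scripted event-screening interview, identical in every arm.
2. **Referral to the committee.** Send every death, hospital admission, unscheduled angiogram and abnormal biomarker to the CEAC automatically, whatever the interviewer's view, in dossiers from which existing study staff have removed the device name.
3. **Study design and overview.** Replace the sentence on the CEAC's blind with one saying that its members are blinded to the allocated device, and make it agree with Treatment assignment.
4. **Reporting.** State that contacts already made were collected unblinded, and describe assessor blinding as covering adjudication, measurement and analysis.

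Recruitment was complete in November 2013, but follow-up runs to 5 years, so the change can still help for the later contacts. It cannot repair the earlier ones. The script does not blind the patient, so some reporting risk remains. The cost is protocol wording, redaction work and more dossiers for the committee. The collection method also changes during follow-up; applied equally to all arms from the same date, this should not itself favour a device. Treatment and sample size are unaffected.
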